| **5- Background and Rationale:**  Globally, prostate cancer (PC) represents the second most frequently diagnosed malignant disease and the sixth leading cause of cancer related death among men and its burden is almost expected to be doubled by 2040 due to population growth and aging [^[[1]](#endnote-1)^]. In Egypt, PC represents 4.5% of male malignancies, but with apparently low incidence and high mortality due to higher prevalence of advanced and metastatic disease [^[[2]](#endnote-2)^,^[[3]](#endnote-3)^]. The treatment of advanced PC is basically dependent on the initial effective responses with androgen deprivation therapy (ADT), through which patients’ progress over time to metastatic castration-resistant prostate cancer (mCRPC). Strategies developed to counteract ADT resistance have had only modest clinical benefit [^[[4]](#endnote-4)^,^[[5]](#endnote-5)^]. Nevertheless, relapsed or metastatic disease following castration has a poor prognosis with most patients dying within two years [^[[6]](#endnote-6)^,^[[7]](#endnote-7)^,^[[8]](#endnote-8)^,^[[9]](#endnote-9)^,^[[10]](#endnote-10)^].  The metabolic effects of ADT, including disturbance of lipid profile leading to increased risk for diabetes, metabolic syndrome and cardiovascular morbidity/mortality may have a role in treatment related morbidity in these patients [^[[11]](#endnote-11)^].  Lipid metabolism is strikingly affected by androgens and dysregulation of lipid metabolism is a key feature of PC development. Androgens may stimulate *de novo* lipogenesis and lipid uptake. HMG coA reductase inhibitors (Statins) are administered widely worldwide for their clinical expressive lipid-lowering effect. Statins not only prevent the production of cholesterol but also block the formation of many intermediary lipid molecules, which might function as cellular signaling pathways stimulant, provoking the major function of cholesterol synthesis in accelerating progression to CRPC.  Several epidemiological reports have shown significant associations between statin use and decreased incidence of advanced PC, risk of recurrence after local treatment, mortality, and PSA levels relative to Statin nonusers [^[[12]](#endnote-12)^,^[[13]](#endnote-13)^].  Statins decrease advanced stage prostate cancer risk raising a possible correlation between cholesterol and prostate cancer risk [^[[14]](#endnote-14)^].  Moreover, high Cholesterol levels have proved to increase the risk of aggressive PC, and according to Jiang and colleagues, statin users after prostatectomy had a less aggressive disease [^[[15]](#endnote-15)^]. Rosuvastatin is the most powerful widely‐prescribed statin worldwide; due to its rapid absorption, achieving peak plasma concentration within three hours. Moreover, its lipid‐lowering effect is not influenced by the time‐of‐day by which it is administered; due to the comparatively long half‐life of 20 hours [^[[16]](#endnote-16)^,^[[17]](#endnote-17)^]. |
| --- |
| **6- Objectives:**  This study aims to investigate, on mechanism-based, the possible therapeutic effects of rosuvastatin when combined with androgen deprivation in metastatic prostate cancer patients. |
| **7- Study Design :**  Prospective study, a patient cohort will be selected according to the following criteria (According to the institutional review board of the NCI): Newly diagnosed cancer prostate patients over 50 years old who will be under primary intervention with surgical castration. Statin will be used at the time of castration. Patients will be classified into two groups treated with castration with or without Rosuvastatin 20 mg/day. |
| **8- Study Methodology:**   1. Population of study &disease Condition   A cohort of 80 patients will be selected according to the following criteria (According to the institutional review board of the NCI): Newly diagnosed cancer prostate patients over 50 years old who will be under primary intervention surgical castration. Statin will be used at the time of castration. Patients will be classified into two groups treated with castration with or without Statin. Using power 85% and 5% significance level, 35 patients are required. |
| b) Back ground and Demographic characteristics   - Male - Over 50 year old   Metastatic prostate cancer |
| c) Inclusion criteria:  Naïve newly diagnosed with metastatic prostate cancer  ▪ Age ≥ 50 years.  ▪ No psychological or geographical barriers for regular follow up of the patients. |
| d) Exclusion criteria:  ▪ Age < 50 years.  ▪ psychological or geographical barriers for regular follow up of the patients. |

| e) Interventions:  Rosuvastatin 20 mg/day for 6 months will be administered at the time of castration | |
| --- | --- |
| f) Possible Risk: **No** drug interaction |  |
| g) Primary outcome parameter   - Lipid profile and metabolism markers: LDL, cholesterol, triglycerides, HDL, HMG-CoA reductase, ABCA1 , SLDLRP1, AKR1C4. - Tumor aggressiveness markers: PSA, ALP, Caveolin-1, EGFR |  |
| h) Secondary outcome parameters:  Short term clinical outcome in terms of disease progression/regression and overall survival |  |
| i) Sample size  A cohort of 80 patients will be selected according to the following criteria (According to the institutional review board of the NCI). Patients will be classified into two groups treated with surgical castration with or without Statin. |  |
| j) Statistical analysis:  Randomization, data management and statistical analysis were performed using The Statistical Package for Social Sciences (SPSS) version 24. Normal distribution and variance homogeneity of data were assessed using the Kolmogorov–Smirnov and Levene’s tests, respectively.  Numerical data were summarized using median and interquartile range (IQR). Categorical data were summarized as count and percentage. Patients were stratified according to their clinicopathological factors and for more than two subgroups of patients, the change in measured parameters were tested for significance using Kruskal–Wallis test and the pairwise comparison were done using Mann–Whitney. The change in proteins concentration over time was tested using Friedman test of significance. Spearman correlation analysis was used to test all possible correlations. Kaplan- Meier survival analysis was used to calculate the cumulative survival rate as well as median levels of OS after two years of follow up. OS was calculated from date of diagnosis to date of death by any cause. Living patients or patients lost to follow-up were censored on the last known alive date. The hazardous effect of death or progression Cox proportion hazard Model was used to evaluate the hazardous effect of different clinicopathological and proteins levels on death and progression. All P-values are two-sided. P-values < 0.05 were considered significant. Patients were equally allocated between the two study arms, but ten patients from the control group lost follow-up and were excluded from all tests. |  |
| k) Source of funding: Cairo University |  |

| **9-Ethical committee approval:**  The study ID BB1901-30303 was approved by the Institutional Human Research Ethics Committee of NCI, Egypt, Number 00004025, with IRB review Number 201819019.3 |
| --- |
| **10- Cooperation with other departments:**  Name of department : Medical Oncology  Name of investigator: [name]  Name of department : Surgical Oncology  Name of investigator: [name]  Name of department : Biostatistics and Cancer Epidemiology  Name of investigator: [name] |

1. [] Ferlay J, Ervik M, Lam F, Colombet M, Mery L, Piñeros M, et al. Global cancer observatory: cancer today. International Agency for Research on Cancer, Lyon, France, 2018. <https://gco.iarc.fr/today>  [↑](#endnote-ref-1)

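### Section 8(j) tests twelve markers across an unlisted set of clinicopathological factors, with pairwise follow-up, all at P < 0.05 and with no stated control of the subgroup error rate

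*Protocol*

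**What the plan says.** Section 8(g) of the protocol names two sets of primary outcome markers. The lipid and metabolism set has eight: "LDL, cholesterol, triglycerides, HDL, HMG-CoA reductase, ABCA1 , SLDLRP1, AKR1C4". The second set has four: "Tumor aggressiveness markers: PSA, ALP, Caveolin-1, EGFR". That makes twelve.

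Section 8(j) describes the subgroup analysis. It divides the men by clinicopathological characteristics and, where this yields three or more groups, "the change in measured parameters were tested for significance using Kruskal–Wallis test and the pairwise comparison were done using Mann–Whitney". The factors are not named, and neither their number nor their levels is given. The section does not say whether the two arms are pooled for these tests.

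A single decision rule covers everything in the section: "All P-values are two-sided. P-values < 0.05 were considered significant". No multiplicity adjustment is mentioned, nothing makes the Mann-Whitney tests depend on a significant Kruskal-Wallis result, and nothing ranks the subgroup tests below other analyses.

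**The concern.** Each marker is tested against each factor, and each such test can be followed by comparisons of every pair of subgroups. A flat 5% threshold limits the error of one test, not of the family. With twelve markers the family is large even for one factor, and it grows with every factor added.

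The practical risk is that chance differences in marker change between, say, grade or stage groups are reported as significant. The subgroups are small: 70 analysed patients give about 70/3 = 23 men per level for a three-level factor and 70/4 = 17.5 for a four-level one, if arms are pooled and levels are equal. Any difference that reaches P < 0.05 at that size will look large.

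This family is separate from the choice among primary markers and from the Spearman correlations in the same section. Dealing with either of those would leave it as it is.

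**Working it through.** The plan gives no error rate for this family other than the 0.05 threshold, so there is no figure of its own to reproduce. Its sample-size statement gives no effect size or standard deviation, cannot be reproduced, and does not bear on the subgroup tests.

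**Inputs from the protocol**
- Threshold: 0.05, two-sided, for all tests (8(j)).
- Markers: 8 + 4 = 12 (8(g)), taken as the measured parameters of 8(j).
- Analysed patients: 80 planned, allocated equally, so 40 and 40. Section 8(j) excludes ten controls from all tests, leaving 40 + 30 = 70.

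**Assumptions, because the protocol is silent**
- One or three factors, independent of each other.
- Three equal levels per factor (four in one check).
- Arms pooled.
- Correlation between marker changes from 0 to 0.8.
- No factor truly affects any marker.

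**Step 1: one marker, one factor.** Three levels give 3 pairs and four levels give 6. If the pairs were independent, the chance of a false result would be 1 − 0.95³ = 0.143 and 1 − 0.95⁶ = 0.265. The pairs share patients, so the true values are lower: simulation gives about 12% and 20%. If a pairwise test is allowed only after a significant Kruskal-Wallis test (called gated below), no false pair can be declared unless that test is itself falsely significant, and the error is about 5%.

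**Step 2: twelve markers, Kruskal-Wallis only, independent tests.** With F factors the chance of at least one false result is 1 − 0.95^(12F).
- F = 1: 1 − 0.95¹² = 0.46, with 12 × 0.05 = 0.6 false results expected.
- F = 3: 1 − 0.95³⁶ = 0.84, with 36 × 0.05 = 1.8 expected.

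Ungated pairwise tests on one three-level factor add up to 12 × 3 = 36 comparisons, with 36 × 0.05 = 1.8 false pairs expected.

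**Step 3: allow for correlated markers.** Simulation of 2,500 null trials per setting, 70 patients, three-level factors; chance of at least one false finding:

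| Tests | Factors | Correlation 0 | 0.5 | 0.8 |
|---|---|---|---|---|
| Kruskal-Wallis only | 1 | 44% | 33% | 21% |
| Kruskal-Wallis only | 3 | 83% | 70% | 50% |
| Pairwise, ungated | 1 | 77% | 62% | 41% |
| Pairwise, ungated | 3 | 99% | 95% | 79% |

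The Kruskal-Wallis rows also serve for gated pairwise testing, since the gate lets nothing through unless Kruskal-Wallis is significant.

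A second simulation (1,000 trials per setting, correlation 0.6 to 0) gave 29-45% and 64-82% for Kruskal-Wallis only, and 55-78% and 92-99% with ungated pairwise tests added. A third, over correlation 0.8 to 0, gave 19-45% and 46-83% gated, and 39-76% and 78-99% ungated. The rounded ranges in the verdict cover correlation 0.8 to 0.

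**Step 4: what full control would require.** The Bonferroni level, which is also Holm's first step, over the Kruskal-Wallis tests is 0.05/12 = 0.0042 for one factor and 0.05/36 = 0.0014 for three.

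**The case against.** The strongest objection is that this is silence, not error. Gating, post-hoc adjustment, the factor list and exploratory labels often sit in a statistical analysis plan, and that plan is not at hand. This stands in part: that the tests are unadjusted is inferred from the absence of any adjustment together with the flat threshold. But section 8(j) does not leave the matter open. It names the tests and applies one threshold to all P-values. A separate plan that adjusted them would conflict with 8(j), which would still need amending.

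The second objection is that Kruskal-Wallis followed by pairwise tests is naturally read as an omnibus test with post-hoc comparisons. On that reading the error within one marker and one factor is about 5%. This is correct, and a reader should not infer that the 5% level necessarily fails within each marker. The excess over markers and factors remains: even gated, one factor carries about 20% or more.

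Three stronger readings are tempting and are not supported.
- A false finding is near certain. That takes about three factors without a gate or about five with one, and the protocol gives no number.
- Every clinicopathological subgroup is tested. The text does not say so.
- The tests would show who benefits from rosuvastatin. That needs a treatment-by-subgroup comparison, and 8(j) describes only marker change across patient factors.

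Finally, these are not the comparison of rosuvastatin with control, and strict error control of descriptive subgroup work in a small mechanistic study is optional. That is fair, and it is why an exploratory label is an adequate remedy. The current text gives no such label.

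**Conclusion.** The concern holds as a badly fixed decision rule. With no true effect, the chance of at least one false subgroup finding is:
- about 20-45% for one factor and 46-83% for three, if pairwise tests follow only a significant Kruskal-Wallis test;
- about 40-77% and 78-99%, if they do not.

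Within one marker and one factor it is about 5% gated, and about 12% (three levels) or 20% (four levels) ungated.

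These figures assume 70 pooled patients, twelve markers, equal three-level factors unless stated, and marker correlation from 0.8 to 0. The number of factors is the most influential unknown. The conclusion does not turn on it, nor on whether the pairwise tests are gated: the lowest value, for one factor with highly correlated markers and gated tests, is still about four times the 5% threshold.

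**What to change.** Amend section 8(j) as follows.

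1. Label the clinicopathological subgroup tests exploratory and exempt them from the rule that calls any P-value below 0.05 significant.
2. Run pairwise comparisons only after a significant Kruskal-Wallis test for that marker and factor, and report Holm-adjusted P-values. The gate alone is not enough with four levels: if one level truly differs, the gate tends to open and the three null pairs among the other levels are left unadjusted.
3. If any subgroup result is to be claimed, list all factors tested and apply Holm, or a stated false-discovery rate, to the Kruskal-Wallis P-values over markers by factors.

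The cost is a few sentences and no extra patients or data. Fewer subgroup results will be called significant. Section 8(j) is written in the past tense and already reports exclusions ("Patients were equally allocated between the two study arms, but ten patients from the control group lost follow-up and were excluded from all tests"), so the analysis may have been done. In that case a factor list fixed in advance may no longer be possible. Item 3 therefore asks for all factors tested, and any subgroup P-values already computed must be re-adjusted.

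### Section 8(j) names no marker test with treatment arm as a factor, so the listed tests cannot separate rosuvastatin from castration on the 12 primary markers

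*Protocol*

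**What the plan says.** Section 6 of the protocol sets the aim as "the possible therapeutic effects of rosuvastatin when combined with androgen deprivation in metastatic prostate cancer patients". Section 7 gives a controlled design: "Patients will be classified into two groups treated with castration with or without Rosuvastatin 20 mg/day". On timing it adds "Statin will be used at the time of castration".

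Section 8(g) lists 12 primary markers. Eight are lipid and metabolism markers ("LDL, cholesterol, triglycerides, HDL, HMG-CoA reductase, ABCA1 , SLDLRP1, AKR1C4") and four concern the tumour ("Tumor aggressiveness markers: PSA, ALP, Caveolin-1, EGFR").

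Section 8(j) then lists the tests:

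- Kruskal-Wallis with pairwise Mann-Whitney on change in the measured parameters. The grouping is given as "Patients were stratified according to their clinicopathological factors and for more than two subgroups of patients".
- Friedman: "The change in proteins concentration over time was tested using Friedman test of significance".
- Spearman for correlations.
- Kaplan-Meier for overall survival, with no between-group test named.
- Cox regression on clinicopathological factors and protein levels, for death and progression.

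Arms appear in 8(j) only where it reports equal allocation and the exclusion of ten control patients.

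**The concern.** The question is comparative and the design has a castration-only control group, but no listed marker test is said to use that group as the comparator. The one test of change over time looks within patients.

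Every patient is castrated, and in the statin group the drug starts at the same moment. Section 5 refers to "The metabolic effects of ADT, including disturbance of lipid profile", so the protocol itself expects markers to move in both arms whether or not the statin works. A test that asks only whether a marker changed cannot say how much of the change is due to rosuvastatin. What is at stake is whether the trial's stated analysis answers its stated question on any primary outcome.

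**Working it through.** **1. Is arm named anywhere?** Going through 8(j):

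| Test | Factor or covariate stated | Arm named? |
|---|---|---|
| Kruskal-Wallis, then Mann-Whitney | clinicopathological subgroups, where there are more than two | no |
| Friedman | time | no |
| Spearman | none | no |
| Kaplan-Meier | none | no |
| Cox | clinicopathological factors, protein levels | no |

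Treatment has exactly two groups, so a sentence about more than two subgroups does not naturally describe the arm comparison. Friedman is stated only for proteins. LDL, cholesterol, triglycerides and HDL, four of the 12 markers, therefore have no stated over-time test.

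**2. Does the sample size reveal an intended comparison?** Section 8(a) says 35 patients are needed at 85% power and 5% significance, without endpoint, effect, SD or test. The figure cannot be reproduced, only inverted. Two-sided, z(0.975) + z(0.85) = 1.960 + 1.036 = 2.996.

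- 35 per arm: d = 2.996 × √(2/35) = 0.72
- 35 in total over two arms: d = 2.996 × √(2/17.5) = 1.01
- 35 patients compared with themselves: dz = 2.996 / √35 = 0.51

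A within-patient reading fits as well as a between-arm one, so the figure does not settle the matter.

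**3. What each test responds to.** With n patients and k visits, Friedman ranks each patient's own visits and computes

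χ² = 12 / [n k (k+1)] × Σ Rⱼ² − 3n(k+1),

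where Rⱼ is the rank sum at visit j. Arm does not enter. Write C for the change due to castration and S for the change due to the statin, taken as additive:

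- Friedman in the statin arm responds to C + S.
- Friedman in the control arm responds to C.
- Friedman on 40 + 30 pooled patients responds to roughly C + (40/70)S = C + 0.57S.
- A comparison of change between arms responds to (C + S) − C = S.

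Only the last isolates the statin.

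**4. Illustration with S = 0.** From the document: 80 patients equally allocated gives 40 and 40, and ten excluded controls leave 40 vs 30. Assumed, because the document gives no figures: 3 visits, normal data, within-patient correlation 0.5, the same linear change in both arms, 2000 simulated trials per row. The direction of the change does not matter to Friedman. The arms are independent, so with p₁ and p₂ the rejection rates in the statin and control arms, the chance that they disagree is p₁(1−p₂) + p₂(1−p₁).

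| Common change (SD) | Friedman, statin arm | Friedman, control arm | Friedman, pooled | Arms disagree | Mann-Whitney on change, between arms |
|---|---|---|---|---|---|
| 0 | 5.4% | 5.5% | 5.65% | 10.3% | 5.1% |
| 0.3 | 27.5% | 24.2% | 47.85% | 38.4% | 4.85% |
| 0.5 | 65.9% | 52.25% | 89.0% | 49.3% | 5.2% |
| 0.8 | 96.85% | 91.4% | 99.95% | 11.2% | 6.4% |
| 1.0 | 99.8% | 98.9% | 100% | 1.3% | 3.85% |

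At 0.5 SD: 0.659 × 0.4775 + 0.5225 × 0.341 = 0.315 + 0.178 = 0.493. The statin arm alone is significant in about 31% of trials and the control arm alone in about 18%.

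The last column has a simulation error of √(0.05 × 0.95 / 2000) = 0.5 percentage points per row, and its mean over the five rows is 5.1%. It should not depend on the common change, because that change cancels.

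**The case against.** Several points on the other side stand.

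- Mann-Whitney is on the list and is applied to change in the measured parameters. Run between arms, it would be a valid test. Excluding ten controls from all tests also suggests that the controls belong in those tests. A reader might infer from 8(j) that the arms are never compared and that the data cannot yield a treatment effect. The text does not support that. It supports only that no stated test names arm.
- A reader might also infer that the protocol will credit castration's effect to the statin. It does not say that Friedman is the efficacy test, that it is run by arm, or that significance is contrasted across arms. The misattribution depends on how the results are read.
- The lipid argument and the Friedman test do not fully meet. The background's statement concerns lipids, while Friedman is stated for proteins. Nor does the background say in which direction castration moves the primary markers.
- The simulated sizes are assumptions, and 0.5 SD gives the most disagreement of the values tried. At 1.0 SD both arms are nearly always significant, and a reader who looks at both sees no contrast to credit to the drug. The tilt towards the statin arm at 0.5 SD comes from the unequal numbers. With 40 per arm, each arm alone would be significant in 0.659 × 0.341 = 22% of null trials.

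A further objection is that a statistical analysis plan, not shown here, may name the comparison. That would excuse missing detail. But 8(j) is a specific list of tests, written in the past tense, on a described set of patients. It fixes tests that answer subgroup and within-patient questions and leaves out the one that the objective needs.

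**Conclusion.** The point holds in a limited form. On the text of 8(j), no test of any of the 12 primary markers has treatment arm as factor or covariate, and the list as written cannot separate the statin from castration. This rests on the wording and on the two treatments starting together, not on the simulation.

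The size of any resulting error is conditional. If Friedman results were taken as the drug effect, within one arm or by contrasting arms, the conclusion could be wrong. Under the assumptions above, the arms disagree in about half of null trials at a common 0.5 SD change and in about 1% at 1.0 SD. A between-arm test stays near 5% per marker throughout. These rates illustrate the mechanism and are not estimates for this trial.

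**What to change.** State as the primary marker analysis a between-arm comparison at a named follow-up time, adjusted for the baseline value. ANCOVA would serve, on the log scale or on ranks if the marker is skewed, or a mixed model if there are several follow-up visits. Report the effect estimate with its 95% CI. Apply it to LDL, cholesterol, triglycerides and HDL as well as to the proteins. Use Mann-Whitney on change between arms as the sensitivity analysis, and describe Friedman and the clinicopathological subgroup tests as descriptive.

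The follow-up time has to be stated by the sponsor: section 8(e) gives six months as the duration of treatment, not as a measurement time. The least repair is one sentence naming the between-arm comparison of change. Baseline adjustment is preferable because, with equal variances and baseline correlation r, its variance relative to a change score is (1 + r)/2, which is 0.75 at an assumed r of 0.5.

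The cost is a change of wording and a re-run on the baseline and follow-up values that the over-time test implies are available. The downside is a modelling assumption, which the rank-based sensitivity analysis covers. The fix does not address multiplicity: 12 independent tests at 5% give 1 − 0.95¹² = 46% for at least one false positive, and that needs its own rule.

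### Overall survival is timed from diagnosis, although the arms and study treatment are defined at castration, so absolute survival is likely overstated in both arms

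*Protocol*

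**What the plan says.** Section 8(j), Statistical analysis, fixes the time origin: "OS was calculated from date of diagnosis to date of death by any cause". It reports a Kaplan-Meier cumulative survival rate and "median levels of OS after two years of follow up", censors survivors and patients lost to follow-up when last known alive, and fits a Cox model for the effect of clinicopathological factors and protein levels on death and progression.

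Study treatment begins elsewhere on the time line. Section 8(e): "Rosuvastatin 20 mg/day for 6 months will be administered at the time of castration". Section 7 defines the arms by the same event: "Patients will be classified into two groups treated with castration with or without Rosuvastatin 20 mg/day".

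On allocation, section 8(j) says "Randomization, data management and statistical analysis were performed using The Statistical Package for Social Sciences (SPSS) version 24", without a date, and "Patients were equally allocated between the two study arms, but ten patients from the control group lost follow-up and were excluded from all tests". Section 8(c) admits patients described as "Naïve newly diagnosed with metastatic prostate cancer"; it sets no maximum time from diagnosis to castration. Section 8(h) lists overall survival as a secondary outcome. The protocol gives no delayed entry and no second origin for OS.

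**The concern.** A survival clock should start when a patient comes under study, because only from then can the patient contribute a death. Here the clock starts at diagnosis, but membership of either arm depends on undergoing castration. If entry is at or near castration, the time from diagnosis to entry is free of deaths by construction. An ordinary Kaplan-Meier estimate treats that time as survival and places patients in risk sets before they could have been observed to die.

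The two quantities that section 8(j) undertakes to report, the survival rate and the median, would then be too high in both arms. The time added precedes both castration and rosuvastatin, so it carries no information on their combined effect, which is the objective in section 6. The Cox model could also be affected if time to castration is related to its covariates, such as disease burden, because those factors are not randomised.

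**Working it through.** The protocol has no OS assumption and no diagnosis-to-castration interval, so there is no planned figure to reproduce. The sizes below rest on assumptions, shown as ranges.

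**1. Inputs from the protocol.** OS origin: diagnosis (8(j)). Start of rosuvastatin: castration (8(e)). Arms: defined by castration (7). Patients: 80 (8(i)), equally allocated, so 40 per arm; ten controls excluded (8(j)), leaving 40 − 10 = 30 controls against 40 on rosuvastatin.

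**2. Assumptions.** Exponential survival from castration; a fixed delay g from diagnosis to castration, the same for every patient; entry at castration.

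**3. Effect on absolute survival.** Let S be true survival 24 months after castration. The monthly hazard is h = −ln(S)/24. A patient 24 months after diagnosis has been at risk for only 24 − g months, so the reported value is exp(−h × (24 − g)) = S^((24 − g)/24).

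| True S at 24 months | g = 1 | g = 2 | g = 3 |
|---|---|---|---|
| 50% | 51.5% | 53.0% | 54.5% |
| 60% | 61.3% | 62.6% | 64.0% |

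For example, 0.50^(22/24) = 0.530 and 0.60^(21/24) = 0.640. The median becomes M + g, where M is the median from castration. A 6-month delay with M = 24 would give 0.5^(18/24) = 59.5% and a median of 30 months.

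**4. Effect on a comparison of arms.** Simulation with 40 per arm, control median 24 months from castration, 24 months of follow-up from castration, exponentially distributed delays and 4,000 runs per setting. HR is rosuvastatin against control.

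| True HR | Mean delay, control / rosuvastatin (months) | HR from castration | HR from diagnosis | Rejection rate, castration / diagnosis origin |
|---|---|---|---|---|
| 1 | 2 / 2 | 0.996 | 0.996 | 5.3% / 5.3% |
| 1 | 6 / 6 | 0.999 | 0.998 | 5.5% / 5.5% |
| 0.60 | 2 / 2 | 0.599 | 0.600 | 31.4% / 30.9% |
| 0.60 | 6 / 6 | 0.602 | 0.609 | 30.0% / 28.3% |
| 1 | 1 / 3 | 1.004 | 0.892 | 5.2% / 6.8% |
| 1 | 1 / 4 | 1.000 | 0.835 | 5.3% / 8.9% |

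With equal delay distributions the origin hardly matters to the contrast. With mean delays 2 or 3 months apart, a null effect looks like a benefit.

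**5. Could chance produce such a difference?** With exponential delays of mean 2 months (SD 2), the standard error of the difference in mean delay for 40 against 30 patients is 2 × √(1/40 + 1/30) = 0.48 months. A 2-month difference is 2/0.48, over 4 standard errors. It would need a systematic cause.

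**The case against.** The strongest reply has four parts.

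- **Allocation at castration is an inference.** Section 7 speaks of castration as still to come, so patients could be enrolled before it, and deaths between enrolment and castration could then be observed. This stands as a limit. The death-free interval would then run from diagnosis to enrolment, and could be shorter. It would still be counted as survival.
- **The delay may be short.** Patients are treatment-naive and newly diagnosed, and castration is their primary treatment. Shifts of about 1 to 5 points lie inside one standard error of the estimate: at 50% survival, √(0.25/40) = 7.9 points with 40 patients and √(0.25/30) = 9.1 points with 30. This also stands. However, the shift always goes in the same direction, and the sampling error does not.
- **Treatment effect.** A reader might infer that this origin creates a spurious difference between the arms. The documents do not support that. Under randomisation with similar delays the hazard ratio and type I error barely move, a 2-month imbalance by chance is implausible, and section 8(j) names no survival test between arms. What remains is a conditional risk: the exclusion of ten controls could make the analysed arms differ in delay, and delay could be related to the Cox covariates.
- **Length of follow-up.** A reader might also infer that two years of follow-up means less than two years after treatment. The protocol does not say when follow-up begins. Only a 24-month rate read on the diagnosis clock has that property.

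**Conclusion.** The point holds in a limited form. The protocol states an OS origin that precedes the event defining the arms and starting treatment, and it makes no allowance for delayed entry. If entry is at or near castration, the reported survival rate and median are too high in both arms: by about 1.5 to 4.5 points at two years when the truth is 50%, by about 1 to 4 points when it is 60%, and by the delay itself for the median. These sizes assume exponential survival and a common fixed delay of 1 to 3 months; the real delay is unknown.

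The point does not show a biased treatment comparison. It concerns a secondary outcome and leaves the primary biomarker outcomes untouched. It is worth correcting because the stated rule is avoidable and the correction is cheap.

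**What to change.** In section 8(j), define OS in both arms from the date of randomisation, or from castration if that is the date of allocation, and state which it is. Report 24-month survival with a 95% CI from that date, and use the same origin for progression, for which the protocol gives none.

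If OS from diagnosis is kept as well, analyse it with delayed entry (left truncation) at study entry and label it descriptive. Report the diagnosis-to-castration interval by arm, so that readers can judge whether delays were similar among the patients analysed.

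The cost is a one-line change of definition and a rerun of the survival analyses. This assumes that the randomisation or castration date is recorded, which the protocol does not say but which would be expected, since rosuvastatin starts at castration. There is no added burden on patients.
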